## Abstract

**Background:**

Low back pain, radicular symptoms, and functional impairment are common manifestations of lumbar disc herniation (LDH), which can substantially impair patients' quality of life. Tuina therapy and core stability training are widely used conservative interventions for LDH, often applied as a combination of passive manual therapy and active exercise to alleviate symptoms and improve function. However, most existing clinical studies are limited by small sample sizes and methodological weaknesses, and robust evidence is lacking regarding whether the combined intervention is superior to either therapy alone.

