Core stability training, as a representative form of exercise-based rehabilitation, directly targets the neuromuscular mechanisms underlying spinal stability. It aims to improve coordination and activation of deep stabilizing muscles, thereby enhancing spinal and pelvic stability. By strengthening these muscles, core stability training can reduce excessive loading on superficial lumbar structures and address instability caused by muscle imbalance or fatigue (17, 18). Previous studies have demonstrated that core stability training can significantly reduce pain and improve functional performance in patients with LDH (19, 20). Nevertheless, exercise-based interventions alone may have limited effects on soft tissue relaxation and pain modulation, particularly in the early stages of treatment. Given their distinct yet complementary mechanisms, Tuina therapy and core stability training may exert synergistic effects in the management of LDH. Tuina primarily improves soft tissue condition and alleviates pain, whereas core stability training enhances neuromuscular control and spinal stability. However, current evidence remains insufficient to determine whether the combined intervention is more effective than either therapy alone, particularly in improving lumbar stability and related clinical outcomes.

Consequently, the present study proposes to conduct a randomized controlled clinical trial with blinded outcome assessment and data analysis to further validate the effectiveness of the combined intervention. A combination of musculoskeletal ultrasound, imaging assessments, pressure biofeedback unit assessment, and patient-reported outcome measures will be used to comprehensively evaluate lumbar stability and clinical outcomes. This approach will help determine whether the combined therapy provides superior benefits compared with single interventions.

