### Study design

2.1

This study is a single-center, three-arm parallel explanatory randomized controlled trial conducted in China (Figure 1). A total of 96 patients with LDH will be recruited and randomly allocated in a 1:1:1 ratio to the Tuina group, the core stability training group, or the combined intervention group. Participants who meet the inclusion criteria will be enrolled after providing written informed consent. Participants will be recruited from 15 October 2025 to 1 November 2027 through outpatient clinics, public advertisements, and social media platforms. All three groups will receive an 8-week intervention, administered three times per week, followed by a 1-month follow-up period. Outcome assessments will be conducted at baseline, after 8 weeks of intervention, and at the end of the follow-up period. The intervention duration was determined based on dose–response evidence, direct clinical trials, and prior rehabilitation literature. A recent systematic review and meta-analysis on stabilization-based exercise in patients with chronic low back pain reported that 8–12-week interventions produced the greatest effects on pain reduction (SMD = –0.88) and disability improvement (SMD = –0.85), with high-certainty evidence for disability outcomes (21). Consistent with this evidence, randomized controlled trials in patients with LDH have commonly adopted 8-week core stabilization protocols. An 8-week motor control training program significantly improved pain, disability, and transversus abdominis activation (22), while an 8-week program (three sessions per week) also demonstrated significant improvements in pain, disability, and trunk muscle endurance (23). Accordingly, an 8-week intervention period was selected, representing a commonly adopted duration within the evidence-supported 8–12-week therapeutic window for stabilization-based interventions in LDH. A 1-month follow-up assessment was included to evaluate the short-term maintenance of treatment effects after completion of the intervention, which is consistent with early post-intervention assessment time points used in randomized controlled trials of LDH (24). To enhance methodological rigor and minimize potential bias, blinded outcome assessment and statistical analysis procedures were incorporated into the study design. Outcome assessment and statistical analysis will be performed by two independent researchers who are blinded to group allocation. The primary and secondary outcome measures include musculoskeletal ultrasound, imaging assessments, pressure biofeedback unit assessment, and patient-reported clinical outcomes to comprehensively assess lumbar stability, pain, and functional status. The study protocol was developed in accordance with the SPIRIT guidelines, and the completed SPIRIT checklist is provided as Supplementary Table S1. In addition, a treatment fidelity checklist is provided as Supplementary Table S2 to ensure consistency and quality of intervention delivery.

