### Sample size calculation

2.5

The sample size was calculated using G*Power 3.1. The calculation was based on the primary outcome, namely the muscle activation ratio of the transversus abdominis assessed by musculoskeletal ultrasound. Previous studies in patients with low back pain have reported medium-to-large effect sizes (Cohen's d ≈ 0.71) for changes in transversus abdominis activation following core stability training (30). Furthermore, ultrasound studies in patients with LDH have demonstrated significant alterations in core muscle morphology (31), suggesting that similar or larger effects may be anticipated in this population. Therefore, a conservative effect size of 0.78 was assumed for the present study.The selected effect size was based on previous studies reporting moderate-to-large effects in similar populations and was conservatively estimated.

With a two-sided α of 0.05 and a power (1−β) of 0.80, the required sample size was 27 participants per group. Considering a 15% dropout rate, the final sample size was set at 96 participants, with 32 participants in each group.

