### Statistical analysis

2.11

All statistical analyses will be performed using IBM SPSS Statistics (Version 27.0). Efficacy analyses will follow the intention-to-treat (ITT) principle, including all randomized participants. Continuous variables will be tested for normality and presented as mean ± standard deviation or median (interquartile range), as appropriate, while categorical variables will be expressed as counts and percentages. Baseline characteristics will be summarized descriptively without formal statistical comparisons. Primary and secondary outcomes will be analyzed using linear mixed-effects models, with group, time, and group-by-time interaction as fixed effects and subjects as random effects. Intervention duration (20 vs. 40 min) and baseline values of the outcome measures will be explicitly included as covariates to account for potential confounding effects. Therapist identity will be included as a random intercept to account for potential clustering effects. Model assumptions will be evaluated using residual diagnostics. If significant group-by-time interactions are detected, post-hoc pairwise comparisons with Bonferroni correction will be performed. Missing data will be handled using multiple imputation under the missing-at-random assumption. Safety analyses will include all participants who received at least one treatment, and adverse events will be compared using the chi-square test or Fisher's exact test, as appropriate. Sensitivity analyses, including complete-case analyses, per-protocol analyses, and analyses adjusted for intervention duration, will be conducted to assess the robustness of the primary outcome. All statistical tests will be two-sided, with a significance level set at *P* < 0.05, and 95% confidence intervals will be reported. Effect sizes (e.g., Cohen's d) will also be reported to facilitate interpretation of the clinical relevance of the findings.

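### The 80% power in section 2.5 belongs to one unadjusted two-group test; under the Bonferroni-corrected comparisons in section 2.11 it is about 65% per contrast with 27 evaluable per arm

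*Protocol article*

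**What the plan says.** The trial has three arms, with patients "randomly allocated in a 1:1:1 ratio to the Tuina group, the core stability training group, or the combined intervention group" (section 2.1). Its question is the combination against each component: the Abstract says that "robust evidence is lacking regarding whether the combined intervention is superior to either therapy alone", and the Introduction closes with "This approach will help determine whether the combined therapy provides superior benefits compared with single interventions".

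Section 2.5 sizes the trial on one outcome: "The calculation was based on the primary outcome, namely the muscle activation ratio of the transversus abdominis assessed by musculoskeletal ultrasound". It cites "medium-to-large effect sizes (Cohen's d ≈ 0.71) for changes in transversus abdominis activation following core stability training" and continues: "Therefore, a conservative effect size of 0.78 was assumed for the present study". At two-sided alpha 0.05 and power 0.80, "the required sample size was 27 participants per group", raised to 32 per group (96 in total) for 15% dropout. No test, contrast or multiplicity adjustment is mentioned.

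Section 2.11 fits a linear mixed model with group, time and their interaction, adjusted for the baseline value and for session duration (20 or 40 min). On comparisons between arms it says: "If significant group-by-time interactions are detected, post-hoc pairwise comparisons with Bonferroni correction will be performed".

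**The concern.** The alpha used for sizing is not the alpha at which the arms will be compared. Section 2.5 spends the full 0.05 on one comparison. Section 2.11 never makes a comparison at that level, because every pairwise test follows a significant interaction and carries a Bonferroni correction. The stated 80% therefore describes a test that the trial does not plan to run.

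The stake is interpretation. A reader who takes 80% at face value would give a non-significant comparison more weight against the combination than it deserves. The statement that matters most, superiority over both components, has lower power still, and the article gives no figure for it.

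**Working it through.** **Inputs.** From section 2.5: effect size 0.78 (read as Cohen's d, since the cited value is given as d), alpha 0.05 two-sided, power 0.80, 27 per group, 15% dropout, 32 per group. From section 2.11: preliminary interaction test, then Bonferroni. Three arms give three pairs, so 0.05/3 = 0.0167 each.

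**1. Reproducing the plan's figure.** For a two-sample t-test the noncentrality is d × √(n/2) and df = 2n − 2.
- n = 27: 0.78 × √13.5 = 2.866; critical t (df 52) = 2.007; power 80.3%.
- n = 26: power 78.8%.
- Dropout: 27/0.85 = 31.8, so 32 per group and 96 in total.

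So 27 is the two-group answer. Other readings that were tried do not return it: a one-sided test gives 21, and a three-group ANOVA gives 23 (f = 0.39), 25 (one arm differing by 0.78) or 33 (evenly spaced means with range 0.78).

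**2. Power per contrast at 0.0167.**
- n = 27: noncentrality 2.866 against critical t 2.474 (df 52) gives 65.3%. With variance pooled over three arms (df 78, critical t 2.447) it is 66.2%.
- n = 32: noncentrality 0.78 × √16 = 3.120 gives 74.3% (df 62) or 75.1% (df 93).
- For 80%: n = 36 gives 80.2% and n = 35 gives 78.8%. Then 36/0.85 = 42.4, so 43 per arm and 129 in total.

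**3. Effect of the preliminary test.** In 400,000 simulated three-arm trials (pooled variance, 27 per arm, d = 0.78 against each single therapy), power per contrast was 66.3% without a preliminary omnibus F test and 66.1% with it. Power for both contrasts was 51.4% either way. The F test alone was significant in 83.7%. The simulation used a single-time F test as a stand-in for the interaction test.

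**4. Power for both contrasts.** The two contrasts share the combined arm, so their correlation is 0.5.

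| Rule, d = 0.78 against each | Evaluable per arm | Per contrast | Both |
|---|---|---|---|
| Interaction test, Bonferroni over 3 pairs | 27 | 65-66% | 50-51% |
| Same | 32 | 74-75% | 61-62% |
| Bonferroni over the 2 key contrasts only | 27 | 71-72% | 57-58% |
| Each at 0.05, both required | 27 | 80-81% | 69-70% |

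At the cited d = 0.71 with 27 per arm, power for both is 39-40% under three-pair Bonferroni and 59-60% with each at 0.05. If one single therapy lies halfway (d = 0.39 against it), power for both is about 15% and 28%.

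**5. Baseline adjustment (assumed range).** If 0.78 is on the raw-SD scale and baseline correlates r with the outcome, the working effect is 0.78/√(1 − r²). The article gives no r. With three-pair Bonferroni and 27 per arm:
- r = 0.3: 0.78/0.954 = 0.818, giving 71% per contrast and 57% for both.
- r = 0.5: 0.78/0.866 = 0.901, giving 80% per contrast and 69% for both.

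**The case against.** **The test behind the 27 is not named.** True; it is inferred. But the effect is discussed as Cohen's d, a two-group measure, and the two-group test returns exactly 27.

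**The low figures are one scenario.** This largely stands. Section 2.11 does not say how many pairs are corrected. The intention-to-treat analysis with imputation may retain more information than 27 completers. Baseline adjustment could bring the per-contrast power back to 80% at r near 0.5. That is why ranges are given. Section 2.5, however, claims no such gain and states no correlation, and even at r = 0.5 with 27 per arm the power for both contrasts stays below 80%.

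**Bonferroni after an overall test is valid.** It is, and it is conservative. Nothing here suggests an inflated type I error. The fault is the mismatch with the stated power.

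**Stronger readings that do not hold.** A reader might infer that true power is 51% where 80% was promised. The two are different quantities: section 2.5 speaks of one comparison, the article nowhere requires both contrasts to be significant, and even uncorrected tests give only about 70% for both. A reader might also infer that the plan pays for multiplicity twice. Step 3 shows that the preliminary test costs almost nothing once Bonferroni is applied.

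**The simulated model is not the planned one.** This stands. Session duration is 20 min in both single-therapy arms and 40 min in the combined arm, so it is fully determined by allocation. With that covariate in the model, the combined-versus-single contrasts cannot be separated from it, and none of these powers applies as written.

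**Conclusion.** The point holds as an internal mismatch. The 80% in section 2.5 is the power of one unadjusted two-group comparison, whereas section 2.11 compares arms only with Bonferroni correction. On the article's own inputs the shortfall is about 14 to 15 points per contrast with 27 evaluable (80.3% against 65.3-66.2%) and about 5 points if nobody drops out (about 75% against the stated 80%). Superiority over both components has about 51% to 62% power over that same range of evaluable patients.

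These figures assume correction over three pairs, d = 0.78 against each single therapy for the both-contrasts figure, no gain from baseline adjustment, and a primary model without the duration covariate. They show a misstated power and an unfavourable choice of tests. They do not show an invalid analysis.

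**What to change.** **Section 2.11, primary outcome.** Replace the sentence on interaction and Bonferroni with two pre-specified week-8 contrasts, combined minus Tuina and combined minus core training, each at two-sided 0.05. Superiority over both is claimed only if both are significant. Because both must succeed, no alpha split is needed. Tuina versus core training becomes secondary. Remove session duration from the primary model.

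**Section 2.5.** State that 80% is the power of one unadjusted contrast and that, with 27 evaluable per arm, the power for both is about 70% at d = 0.78 and about 60% at the cited 0.71.

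**If Bonferroni is kept instead,** restate the power as about 65% per contrast (75% with no dropout).

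**Cost.** Wording in two sections and no extra patients. The stated power looks less favourable, and the both-required rule gives no formal claim against one comparator alone. In return, power for the trial's main question rises from about 51% to about 70% on the same data. The change should be fixed before the database is locked.

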## Discussion

3

To our knowledge, this study is among the first randomized controlled trials to investigate the combined effects of Tuina and core stability training in patients with lumbar disc herniation (LDH). Although both interventions are commonly used in clinical practice, high-quality evidence evaluating their combined efficacy remains limited. Given the high prevalence, prolonged disease course, and increasing trend toward younger onset of LDH, there is a need to explore effective and evidence-based rehabilitation strategies (25, 42). Tuina and core stability training may exert complementary effects, with Tuina primarily improving soft tissue mobility and pain, and core stability training enhancing neuromuscular control and spinal stability (18, 43). The combination may therefore provide complementary and potentially synergistic effects. This integrative approach may address both passive tissue dysfunction and active neuromuscular deficits.

This study has several strengths. It employs a randomized controlled design with blinded outcome assessment and data analysis to minimize potential bias. In addition, multiple outcome measures, including musculoskeletal ultrasound, lumbar imaging, and clinical assessments, are incorporated to comprehensively evaluate changes in lumbar stability and function. Importantly, this study focuses on lumbar stability as a core outcome, which has been insufficiently addressed in previous studies. In addition, the inclusion of a follow-up period allows for the assessment of short-term sustainability of treatment effects.

However, several limitations should be acknowledged. This is a single-center study with a relatively small sample size, which may limit generalizability. Blinding of participants and therapists was not feasible due to the nature of the interventions, which may introduce performance bias and expectation effects. Specifically, patient-reported outcomes (VAS, ODI, JOA, and SF-36) may be influenced by participants' perceptions and treatment expectations. To mitigate these biases, objective outcome measures—including musculoskeletal ultrasound, MRI, X-ray, and pressure biofeedback—will be assessed by independent evaluators blinded to group allocation, and statistical analyses will be conducted by investigators blinded to group allocation. Certain measurements, particularly ultrasound assessments, may still be subject to operator-dependent variability (44). Some mechanistic inferences rely on prior literature rather than direct measurement, and the absence of a sham or placebo control may further introduce expectation-related effects. The combined intervention group received twice the total intervention duration compared to monotherapy groups (20 vs. 40 min per session), although intervention duration will be included as a covariate, residual confounding cannot be entirely excluded. The upper age limit of 55 years restricts generalizability to older adults with LDH, and despite standardized training, some operator-dependent variability in Tuina procedures may remain. Future multicenter studies with larger sample sizes, longer follow-up periods, and time-matched control designs are warranted to confirm these findings and isolate the specific effects of the combined intervention. Overall, this study is expected to provide preliminary evidence and methodological guidance for integrating Tuina and core stability training in LDH management.

If proven effective, this combined approach may provide a practical and scalable rehabilitation strategy for patients with LDH in clinical settings.
